## Abstract

**Background:**

The increasing emphasis to share patient data from clinical research has resulted in substantial investments in data repositories and infrastructure. However, it is unclear how shared data are used and whether anticipated benefits are being realized.

**Objective:**

The purpose of our study is to examine the current utilization of shared clinical research data sets and assess the effects on both scientific research and public health outcomes. Additionally, the study seeks to identify the factors that hinder or facilitate the ethical and efficient use of existing data based on the perspectives of data users.

**Methods:**

The study will utilize a mixed methods design, incorporating a cross-sectional survey and in-depth interviews. The survey will involve at least 400 clinical researchers, while the in-depth interviews will include 20 to 40 participants who have utilized data from repositories or institutional data access committees. The survey will target a global sample, while the in-depth interviews will focus on individuals who have used data collected from low- and middle-income countries. Quantitative data will be summarized by using descriptive statistics, while multivariable analyses will be used to assess the relationships between variables. Qualitative data will be analyzed through thematic analysis, and the findings will be reported in accordance with the COREQ (Consolidated Criteria for Reporting Qualitative Research) guidelines. The study received ethical approval from the Oxford Tropical Research Ethics Committee in 2020 (reference number: 568-20).

**Results:**

The results of the analysis, including both quantitative data and qualitative data, will be available in 2023.

**Conclusions:**

The outcomes of our study will offer crucial understanding into the current status of data reuse in clinical research, serving as a basis for guiding future endeavors to enhance the utilization of shared data for the betterment of public health outcomes and for scientific progress.

**Trial Registration:**

Thai Clinical Trials Registry TCTR20210301006; https://tinyurl.com/2p9atzhr

**International Registered Report Identifier (IRRID):**

DERR1-10.2196/44875

## Introduction

### The Value of Clinical Research Data

Although clinical research data are generated to answer specific questions, the data can be used for purposes other than those of the original planned analyses to increase medical understanding and improve the general health of the population [1,2].

Many recent advances in medicine are credited to the reuse of existing research data. During the outbreaks of H1N1; MERS (Middle East Respiratory Syndrome); Ebola; Zika; and, more recently, COVID-19, decision-making authorities such as the World Health Organization depended on the analysis of historical epidemiological and clinical data to understand disease progression patterns and associated risk factors. This knowledge was the basis of recommendations for nonpharmaceutical interventions to control the spread of the diseases [3-6]. Guidelines for treatment therapies and preventive medicines depend on findings from clinical trials. The design and interpretation of these clinical trials rely heavily on data from previous studies in, for instance, the calculation of sample sizes, definition of outcomes, selection of interventions and control treatments, and establishment of follow-up duration [7-10]. Existing clinical research data have also been used to answer completely new research questions for teaching purposes and to reproduce results of published research [11].

As the volume of research data continues to rise, there is greater potential for faster and innovative discoveries in diagnostics and the treatment and prevention of diseases through traditional analyses and machine learning technologies [12].

Recognizing the value of data reuse, funders, journals, and research bodies are establishing policies and making substantial resource investments in infrastructure to facilitate data sharing [13,14]. In 2003, the National Institutes of Health introduced the first funder-driven data sharing policy. By 2016, key health research funders required individual participant-level data that support findings of clinical trials to be made accessible at the time of the publication of study results [15-17]. Journals and publishers followed suit, with the majority of them mandating the inclusion of data availability statements in articles for publication [18]. These statements describe how and when data can be accessed and on which repository data are stored. Numerous repositories have been established by funders, pharmaceutical companies, academic research institutions, governments, and discipline-specific consortia [19]. In 2016, at the G20 Hangzhou Summit, the FAIR (Findable, Accessible, Interoperable, and Reusable) principles were endorsed. The FAIR principles aim to optimize the reuse of data sets by ensuring that data are findable; are accessible; are presented in a standardized, interoperable format; and exist on terms that allow reuse [20,21]. Groups such as the Clinical Data Interchange Standards Consortium have defined standard ways of describing data and metadata [22]. By standardizing data and metadata, researchers and algorithms can correctly interpret data without the need for intermediary translation or curation. Analytical tools, such as TwoRavens [23], now allow users to run statistical models and view summary statistics on data held in repositories. The implementation of this ecosystem requires staff with specialized skills; research institutions are investing in hiring and training data managers, programmers, and data scientists to develop interfaces and curate data and metadata.

It is expected that these investments in infrastructure will increase the usage of existing data and, consequently, generate a rich reference for evidence-based decision-making.

### Rationale

Despite the efforts to facilitate data sharing, it is still unclear if and how shared data sets are used and whether the anticipated benefits are being realized. Previous studies described data usage trends based on data sets held in repositories and those from studies that are registered in clinical trial registries [24]. Negative results and studies terminated prematurely are often not published in repositories, yet data from these studies may hold useful insights for planning future research [25]. A substantial proportion of studies conducted in low- and middle-income countries (LMICs), especially noninterventional studies, are not registered [26]. Data sets generated in LMICs are particularly valuable, given the high disease burden in LMICs and the low volume of research being conducted in these areas [27-30]. To our knowledge, no recently published work has examined current barriers to and opportunities for maximizing data utility in LMICs.

### Objectives

Against this background, our study aims to bridge the evidence gap by (1) characterizing how clinical research data sets are reused; (2) describing what impact, if any, data reuse has had on scientific research and general public health; and (3) defining barriers to and opportunities for promoting the ethical, efficient, and equitable reuse of data based on the perspectives of secondary data users.

As previous studies primarily focused on participants from high-income countries, we will target individuals working with data collected from LMICs for the interviews and aim to include respondents from both high-income countries and LMICs in the survey.

## Methods

### Overview

We will conduct a mixed methods study comprising an anonymous web-based survey and semistructured in-depth interviews. The survey will provide data from a large population, while the interviews will generate data on the detailed and contextualized perspectives of individual data users. We aim to include a wide spectrum of participants to reflect the diversity in research areas, career levels, and geographical locations.

### Recruitment

#### Cross-sectional Survey

We will include at least 400 participants, of whom half will be individuals with a history of data reuse (data users), and the other half will be participants with no history of data reuse (nonusers). For the data user group, we will investigate what kinds of data sets were used, how the data were accessed, the purposes for requesting the data, and outcomes of the secondary analyses. We will additionally probe for information on challenges faced in accessing and using the data. For the nonuser group, we will determine reasons for not using shared data sets and identify perceptions on data reuse.

The inclusion criteria are as follows: (1) individuals aged ≥18 years, (2) researchers and professionals working in clinical research or with clinical research data, and (3) those who provide written consent to participate in the study. Individuals with no access to a computer, a mobile device, or the internet will be excluded, as data collection will be mainly conducted via the internet.

Potential participants will be requested to provide consent by ticking a checkbox to confirm that they agree to participate in the study. Respondents who do not provide consent will not be able to access the survey.

Data users will be directed to a page for data users, while nonusers will be directed to a page for nonusers. It will take 3 to 7 minutes to complete the survey for data users and 1 to 2 minutes to complete the survey for nonusers.

The survey will be designed based on existing literature. A panel of experts will be involved in the survey design, including social scientists and ethicists (for informing how questions are framed), a statistician (for the sampling strategy and the development of measurement scales and scoring schemes), a data manager (for survey development and data extractions), and a group of researchers and data users (for piloting). We will use the cognitive debriefing method to pilot the survey among respondents who are similar to the target population. The pilot testing group will be selected purposively for practical reasons and will include individuals from diverse research areas, career levels, and geographical locations. During the pilot, we will check the comprehension of each question; the ability to recall answers; and whether questions are appropriate, are clear, and have sufficient response options. Feedback from the pilot phase will be incorporated in the final survey before deployment for data collection. To achieve demographic diversity, the survey will be translated into other languages, such as Spanish, French, and Portuguese. We will translate the survey by following the TRAPD (Translation, Review, Adjudication, Pretesting, and Documentation) model [31]. Professional translators will perform the initial translations before a review by bilingual individuals. To guarantee that the translated survey accurately represents the intended meaning, it will be pretested with native speakers who are comparable to the target audience.

The survey instrument focuses on the following four main areas: respondents’ demographics, the nature of data use, challenges with data use, and interventions to enhance data use (Multimedia Appendices 1-5). Conditional logic will be applied to display nested questions that are dependent on the respondents’ previous answers. For example, respondents who have published results that are based on secondary analyses will be asked to indicate the number of publications generated from those analyses. Similarly, questions on the history of data use will not be displayed for nonusers.

To reach the target population, the survey will be advertised on forums for researchers and secondary data users, such as the Global Health Network and the COVID-19 Clinical Research Coalition; in conferences; and through the collaborating institutions’ social media platforms. Participants will also be encouraged to share the survey with their colleagues. The survey will be conducted globally. The data will be reviewed after the number of recruited participants reaches one-third (132/400, 33%) of the target sample size to monitor the distribution of respondents by geographical location, research area, and occupation. The results of the review will be used to strategize the advertisement and distribution of the survey to target specific groups.

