#### Interviews

Semistructured in-depth interviews will be conducted with 20 to 40 data users or until a state of data saturation is reached. Data saturation occurs when further interviews no longer produce new insights or themes [32]. Considering limitations on travel and on holding meetings resulting from the COVID-19 pandemic, we will primarily use web-based or remote methods for data collection. In-person interviews may be conducted when it is safe to do so, in compliance with local regulations.

The inclusion criteria are as follows: (1) individuals aged ≥18 years, (2) researchers or professionals using clinical research data shared by other researchers for secondary purposes, and (3) those who provide consent to participate in the study.

Potential participants will be identified through a web-based search for publications that are based on secondary analyses, focusing on researchers and professionals who have used data from LMICs. The corresponding authors will be contacted by email and invited to participate in interviews. To reach data users who have not yet generated publications, we will invite individuals who have requested data sets from institutional data repositories. Individuals who are interested in participating in the study will be sent the participant information sheet and consent form by email. The information sheet will describe the nature of the study, what the interviews will entail, and details on how data will be stored and processed during and after the study. It will be clearly stated that the participants are free to withdraw from the study at any time, for any reason, and with no obligation to give the reason for withdrawal. The participants will be allowed as much time as they wish to consider the information, and they will be given the opportunity to raise questions with the investigator or other independent parties to decide whether they will participate in the study. Interviews will then be scheduled at mutually convenient times. Audio-recorded consent will be obtained prior to asking the interview questions. The interviewer will document that verbal consent was obtained on a consent form. The investigator will keep a copy of the signed form in the study file and send a copy to the participants by email. For interviews that are held in person, the participants will sign the consent form prior to start of the interview. The interviews are estimated to last 40 to 60 minutes. Multimedia Appendix 6 shows the interview guide.

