### Limitations

The survey participants will be selected by using nonrandom sampling, which means that the results may not accurately reflect the characteristics of the whole population and may be affected by bias in the selection process. Additionally, it is possible that the survey may only reach those who regularly use the web-based platforms where the survey is promoted, potentially resulting in an incomplete representation of the target population. Although it is acknowledged that the survey results may not be generalizable to a larger population, the data from our exploratory study will provide ideas and hypotheses that could guide future research. Additionally, the in-depth interviews are expected to provide valuable and contextualized information.

The study is limited to the description of the current state of data reuse, and it will not explore causal relationships. However, the findings from our study can be used as a foundation to design future studies that establish cause-and-effect relationships in secondary data use and explore perspectives of nonusers.

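### Detailed access-barrier data come from people who obtained data; failed requesters are not separately identified, and the nonuser arm matches no stated objective

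*Protocol article*

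**What the plan says.** **Survey.** The Cross-sectional Survey section plans at least 400 respondents, half with and half without past data reuse. In its description of the user group it states: "We will additionally probe for information on challenges faced in accessing and using the data". For the others: "For the nonuser group, we will determine reasons for not using shared data sets and identify perceptions on data reuse". Routing is two-way: "Data users will be directed to a page for data users, while nonusers will be directed to a page for nonusers". The user page is expected to take 3 to 7 minutes and the nonuser page 1 to 2 minutes.

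**Interviews.** The second inclusion criterion in the Interviews section admits "researchers or professionals using clinical research data shared by other researchers for secondary purposes". The same section adds a recruitment route: "To reach data users who have not yet generated publications, we will invite individuals who have requested data sets from institutional data repositories". The Abstract and the Methods overview also describe interviewees as people who have used data.

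**Objectives and limitations.** Objective 3 is "defining barriers to and opportunities for promoting the ethical, efficient, and equitable reuse of data based on the perspectives of secondary data users". The Limitations section acknowledges nonrandom sampling and reliance on web platforms. It then says the findings can support future studies that "establish cause-and-effect relationships in secondary data use and explore perspectives of nonusers".

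**The concern.** Sorting respondents by past reuse conditions the detailed access questions on an outcome that access barriers themselves affect. A refusal, an abandoned application or an unacceptable condition of access can be what makes someone a nonuser. The people who met the most effective barriers are then the ones described as receiving the shorter page, and they do not qualify for interview.

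This matters for how the results are read. The Conclusions section wants the findings to inform strategies for increasing use of existing data sets. A profile of access problems drawn from users may under-represent the problems that stop use altogether, and a larger sample would not change that.

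There is also a plain inconsistency. Half of the minimum sample consists of nonusers whose reasons and perceptions are to be collected, yet no objective names them and the Limitations section treats their perspectives as future work.

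**Working it through.** **1. The plan's own figure.** Inputs from the Sampling section: 200 per group, prevalence 50%, 95% confidence, precision around 7%.

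Half-width = 1.96 × √(0.5 × 0.5 / 200) = 0.0693, or 6.9 points. Inverted at 7 points: 1.96² × 0.25 / 0.07² = 196. The stated 200 per group reproduces. The figure describes sampling error only.

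**2. A failed requester followed through the plan.**

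- Survey: no past reuse, so on the description given this person goes to the nonuser page. The access-challenge probe is described for users. The nonuser page asks for reasons and perceptions, so a refusal can be reported there, but nothing described marks who had tried.
- Interviews: the person may be on a repository request list and be invited, but is not using shared data and so does not meet the second criterion. The recruitment sentence treats requesters as users who have not yet published, which is not true of every requester.
- Limitations: general selection bias is named; selection on having obtained data is not.

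**3. Possible size (all inputs assumed).** Let f be the share of people who tried and never obtained data, pF the share of them reporting a given barrier, and pS the share of successful users reporting it.

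Rate among all who tried = (1 − f) × pS + f × pF. A user-only rate is lower than this by f × (pF − pS).

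| f | pS 50%, pF 70% | pS 50%, pF 90% | pS 30%, pF 90% |
|---|---|---|---|
| 5% | 1 point | 2 | 3 |
| 10% | 2 | 4 | 6 |
| 20% | 4 | 8 | 12 |
| 30% | 6 | 12 | 18 |
| 40% | 8 | 16 | 24 |

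Seven of the 15 cells exceed the planned precision of about 7 points; eight do not.

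**4. What a separate group would deliver.** If 5%, 10%, 20% or 30% of the 200 nonusers had tried and failed (assumed), that is 10, 20, 40 or 60 people. Half-width = 1.96 × √(0.25 / m), which gives about 31, 22, 15 and 13 points.

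**5. Objectives against the nonuser arm.** Objective 1 concerns how data are reused, objective 2 the impact of reuse, and objective 3 barriers as users see them. None covers the 200 nonusers, while the survey section sets out to learn their reasons and perceptions and the Limitations section defers those perspectives.

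**The case against.** The strongest reply is that the survey already contains the people in question. Nonusers are half the minimum sample and are asked why they have not used shared data, so a refused requester is eligible and can say so. Users can also report other requests of theirs that failed. This stands. A reader might infer that barriers are measured only, or mainly, in people who overcame them; the documents do not support that.

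Second, the instruments are in appendices that are not shown. The nonuser page may list refusal among its reasons, and the screening question may be finer than the article suggests. This also stands, and the point is limited to what the article describes.

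Third, restricting barriers to users' perspectives is a declared scope, repeated in the Abstract, the Objectives and the Expected Findings, and the interview criterion is consistent with it. A rate-type bias also does not carry over directly to purposive thematic interviews. It would therefore go too far to say that objective 3 is compromised. What the declared scope does not do is explain the nonuser arm, or tell readers that the detailed access data are conditional on having obtained data.

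Fourth, the Limitations section already concedes selection bias and limited generalizability. That is partial cover: it names recruitment channels, not this mechanism.

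On the deferral of nonuser perspectives, one could read it as meaning in-depth perspectives only. The sentence does not say that.

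**Conclusion.** The point holds in a limited form. As described, the detailed access-challenge items and all interviews are conditioned on having obtained data, failed requesters are not separately identified, and the Limitations do not disclose this. Barriers that block reuse are captured in less detail, though not missed.

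The size is unknown. Step 3 gives about 1 to 24 points, resting on assumed f of 5% to 40% and three assumed pairs of barrier rates. A reader could build a striking single example: if 30 of 100 requesters fail and all 30 met a barrier, against 21 of the 70 who succeed, the rates are 21/70 = 30% among users and (21 + 30)/100 = 51% among all who tried. Nothing in the documents supports those inputs, so it should not be taken as an estimate, nor should it be said that rates will be understated by any particular amount.

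The mismatch between the nonuser arm, the objectives and the Limitations sentence needs no assumption and should be reconciled.

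**What to change.** 1. Add one routing question for nonusers: have they ever requested or tried to obtain shared data (yes/no)? Show those answering yes the access-challenge items and report them as a separate group beside the users. Do not pool the two into a rate among everyone who tried: the half-and-half split is set by design in a nonprobability sample, so a pooled rate would reflect recruitment rather than the population.
2. Add nonusers' reasons and perceptions to objective 3, and correct the Limitations sentence that leaves them to future studies.
3. State in the Limitations that the interviews and the detailed access items are conditioned on having obtained data. Reconcile the requester recruitment route with the second interview criterion, at least by saying that requesters will be screened for actual use. Widening the criterion to requesters is optional, since it changes the question asked.

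Cost: one extra item to translate and pretest in five languages, a slightly longer nonuser page, and a subgroup that is likely to be small and imprecise (step 4). Items 2 and 3 are text changes and can be made even if the survey is already in the field.
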